| **Is experience of practising in UK primary care available within the research team?**  *No but we have ready access to advice from GPs within our Department.* |  |  |
| 1. **References relating to your study**   Please list up to 3 references (most relevant) relating to your proposed study:   1. Forster AS, Burgess C, Dodhia H, Fuller F, Miller J, McDermott L, et al. Do health checks improve risk factor detection in primary care? Matched cohort study using electronic health records. Journal of Public Health. 2015:fdv119. 2. Cochrane T, Davey R, Iqbal Z, Gidlow C, Kumar J, Chambers R, et al. NHS health checks through general practice: randomised trial of population cardiovascular risk reduction. BMC public health. 2012;12(1):944. 3. Artac M, Dalton AR, Majeed A, Car J, Millett C. Effectiveness of a national cardiovascular disease risk assessment program (NHS Health Check): results after one year. Preventive medicine. 2013;57(2):129-34. | | |
| **Section C: Access to the data** | | |
| 1. **Financial Sponsor of study**   Pharmaceutical Industry  *Please specify:*      Academia  *Please specify:*  Government / NHS  *Please specify:*      Charity *Please specify:*  Other  *Please specify:*[name] is supported by the Saudi Arabia Ministry of Health None | | |
| 1. **Type of Institution carrying out the analyses**   Pharmaceutical Industry *Please specify:*      Academia *Please specify:* King’s College London  Government Department *Please specify:*      Research Service Provider *Please specify:*  NHS *Please specify:*      Other  *Please specify:* | | |
| 1. **Data source**   The sponsor has direct access to CPRD GOLD and will extract the relevant data*    A data set will be supplied by CPRD**  CPRD has been commissioned to extract the relevant data and to perform the analyses  Other *Please specify:*    *If data sources other than CPRD GOLD are required, these will be supplied by CPRD  ** Please note that datasets provided by CPRD are limited in size. Applicants should contact CPRD ([[contact]](mailto:[contact])) if a dataset of >300,000 patients is required. | | |
| 1. **Primary care data** (please specify which primary care data set(s) are required)   Vision only (Default for CPRD studies)  EMIS® only*  Both Vision and EMIS®*  *Note: Vision and EMIS are different clinical systems, Vision data has traditionally been used for CPRD, EMIS is currently undergoing beta-testing.*  **Investigators requiring the use of EMIS data must discuss the study with a member of CPRD staff before submitting an ISAC application*  Please list below the name of the person/s at the CPRD with whom you have discussed your request for EMIS data: | | |
| **Section D: Data linkage** | | |
| 1. **Does this protocol also seek access to data held under the CPRD Data Linkage Scheme?**   Yes*  No  If No, please move to section E.  **Investigators requiring linked data must discuss the study with a member of CPRD staff. It is important to be aware that linked data are not available for all patients in CPRD GOLD, the coverage periods for each data source may differ and charges may be applied. Please contact the CPRD Research Team on [contact] or email* [*[contact]*](mailto:[contact]) *to discuss your requirements before submitting your application.*  Please list below the name of the person/s at the CPRD with whom you have discussed your request:  [name], Research Statistician, CPRD  *Please note that as part of the ISAC review of linkages, the protocol may be shared - in confidence - with a representative of the requested linked data set(s) and summary details may be shared - in confidence - with the Confidentiality Advisory Group of the Health Research Authority.* | | |
| 1. **Please select the source(s) of linked data being requested:**   ONS Mortality Data  NCDR Cancer Registry Data*  Inpatient Hospital Episode Statistics  MINAP  Outpatient Hospital Episode Statistics  Mother Baby Link    Index of Multiple Deprivation  Townsend Score  Other** *Please specify:*  **Please note that applicants seeking access to cancer registry data must provide consent for publication of their study title and study institution on the UK Cancer Registry website. They must also complete a* ***Cancer Dataset Agreement Form*** *(available from CPRD) and provide a* ***System level Security Policy*** *for each organisation involved in the study.*  *** If “Other” is specified, please name an individual in CPRD that this linage has been discussed with.* | | |
| 1. **Total number of linked datasets requested including CPRD GOLD**: 3 | | |
| 1. **Is linkage to a local dataset with <1 million patients being requested?**   Yes*  No  ** If yes, please provide further details:* | | |
| 1. **If you have requested linked data sets, please indicate whether the Chief Investigator or any of the collaborators listed in response to question 5 above, have access to any of the linked datasets in a patient identifiable form, or associated with a patient index.**   Yes*  No  ** If yes, please provide further details:* | | |
| 1. **Does this study involve linking to patient *identifiable* data from other sources?**   Yes  No | | |
| **Section E: Validation/verification** | | |
| 1. **Does this protocol describe a purely observational study using CPRD data (this may include the review of anonymised free text)?**   Yes*  No**  ** Yes: If you will be using data obtained from the CPRD Group, this study does not require separate ethics approval from an NHS Research Ethics Committee.*  *** No: You may need to seek separate ethics approval from an NHS Research Ethics Committee for this study. The ISAC will provide advice on whether this may be needed.* | | |
| 1. **Does this study require anonymised free text?**   Yes*  No  **Please note that work involving free text can only be performed on the July 2013 CPRD GOLD database build or earlier versions. CPRD can provide further advice on the use of anonymised free text.* | | |
| 1. **Does this protocol involve requesting any additional information from GPs?**   Yes*  No  * *Please indicate what will be required:*  Completion of questionnaires by the GP** Yes  No  Provision of anonymised records (e.g. hospital discharge summaries) Yes  No  Other (please describe)  * Any questionnaire for completion by GPs or other health care professional must be approved by ISAC before circulation for completion.* | | |
| 1. **Does this study require contact with patients in order for them to complete a questionnaire?**   Yes*  No  **Please note that any questionnaire for completion by patients must be approved by ISAC before circulation for completion.* | | |
| 1. **Does this study require contact with patients in order to collect a sample?**   Yes*  No  ** Please state what will be collected:* | | |
| **Section F: Signatures** | | |

**Long-term outcomes of NHS Health Checks in England.**

1. **Lay Summary (Max. 200 words)**

The NHS Health Check (NHSHC) is a primary prevention programme aimed at reducing important causes of mortality in England. The programme targets individuals aged 40 to 74 years and estimates their risk of heart disease, stroke, type 2 diabetes, chronic kidney diseases and some forms of dementia. After identifying individuals at elevated risk, a personalised risk management intervention is provided. As part on ongoing evaluation of the programme’s outcomes, we aim to use CPRD data to evaluate the long-term impact of the NHSHC programme, since its introduction in 2009. In this study, we aim to evaluate changes in risk factors, risk factor management, occurrence of strokes and heart attacks and mortality outcomes. This will be done by comparing these measures between a sample who participated in the health check programme and a matched control who did not initially receive a health check. The results will provide a non-randomised assessment of the programme’s effectiveness through continuing monitoring and evaluation.

1. **Technical Summary (Max. 200 words)**

A new programme of NHS Health Checks (NHSHC) was introduced in the UK in 2009. This aims to provide cardiovascular risk assessment every five years for adults aged 40-74 who are not already diagnosed with CVD or diabetes. The NHSHC offers a promising strategy for preventing CVD, yet several concerns have been raised in relation to its uptake, cost-effectiveness, success in reducing diseases and effectiveness of risk management. In this context, evaluation of the programme’s longer-term outcomes is crucial. This study aims at evaluating changes in risk and cardiovascular clinical events and mortality outcomes following uptake of a health check. We will use a matched cohort design in the CPRD by comparing participants with a record of a complete NHSHC between 1st of April 2010 and 31st of March 2013 with follow-up data available for a minimum of three years after their health check up to 31st March 2016, together with matched control participants who did not receive a health check. We will adopt a time-to-event framework with date of check as the start date to evaluate the onset of new prescriptions. Hazard ratios will be estimated using the cox proportional hazards model and incident rate ratios using Poisson regression to examine the association between the programme and changes in clinical events and mortality.

1. **Objectives, Specific Aims and Rationale**

**Aim:** To measure the long term outcomes of the NHS Health Checks programme and evaluate whether outcomes following an NHS Health Check are more favourable than in controls.

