**Objectives:**

1. To test the hypotheses that greater changes in CVD risk factors, CVD risk score and CVD risk management follow the NHS Health Check than are observed in control participants;
2. To test the hypothesis that all-cause mortality and the incidence of clinical events (new diagnoses of ischaemic heart disease, stroke, diabetes mellitus and chronic kidney disease) may be lower in participants who received NHS Health Checks than control participants;
3. To test the hypothesis that inequalities in the outcomes of Health Checks across deprivation category may be lower in NHS Health Check participants than in control participants.
4. **Background**

Cardiovascular disease is the leading cause of death worldwide and in the United Kingdom (1). Almost 155,000 deaths annually are caused by CVD in UK, accounting for more than a quarter of all deaths (2). Diabetes also is increasing in frequency, with four million people in UK living with diabetes, which is associated with serious complications leading to disability and premature mortality (3).The NHS Health Check (NHSHC) is a primary prevention programme that was introduced in England. The programme targets individuals aged 40 to 74 years, who have not yet developed CVD and are not treated for elevated risk, and estimates their risk of heart disease, stroke, type 2 diabetes, chronic kidney diseases and some forms of dementia (4). After identifying individuals at elevated risk, a personalised risk management intervention is provided. This programme provides an opportunity in terms of addressing multiple risk factors which, if successful, might reduce the risk of several diseases. Results from the Department of Health economic model suggested that the NHS Health Check could save 650 lives, and 1600 heart attacks and 4000 cases of diabetes could be prevented a year (5).

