The original sample was extracted from the October 2014 release of CPRD for 140,356 participants with a record of an NHS Health Check between 1 April 2010 and 31 March 2013, from 452 general practices in England. We restricted the sample to all 106,784 participants registered with 334 general practices with IMD 2010 quintile for England, linked via the participant postcode, at the lower super-output area level. We also excluded all patients who were ever treated with antihypertensive drugs (8531) or statins (1529) before the date of the check. We also excluded patients (4859) who did not have a full year of up to standard record before the date of the check and one patient whose check was after 31 March 2013. We also excluded patients with diabetes (227), coronary heart disease (2) or stroke (3) diagnosed before the check. There remained 91,618 participants who had a health check between 1 April 2010 and 31 March 2013, who had at least 12 months record, were never treated with antihypertensive drugs or statins, and were not diagnosed with diabetes, stroke or CHD before the check. For these 91,618 participants, eligible control participants were identified for 75,123 (82%) and these participants, and their matched controls, will be included in the present study.

1. **Selection of comparison group(s) or controls**

Control participants were selected if they were eligible for the NHS Health Checks but did not receive the check, they might have been invited to attend the Health Check, or not. The control participants were individually matched by general practice, gender and age with participants who received the Health Check.

1. **Exposures, Outcomes and Covariates**

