**Table 1: Case definitions for key measures:**

| **Condition** | **Read Codes** | **Therapy Codes** | **Test results** | **ICD-10 codes** |
| --- | --- | --- | --- | --- |
|  |  |  |  |  |
| **Ischaemic heart disease** | As listed in reference 9. | N/A | N/A | I20-I25 |
|  |  |  |  |  |
| **Stroke** | As listed in reference 10. | N/A | N/A | I60-I64 |
|  |  |  |  |  |
| **Diabetes mellitus** | As listed in Appendix 1. | BNF chapter 6.1.1 and 6.1.2 | HbA1c >=6.5% (48 mmol/mol) | E10-E14 |
|  |  |  |  |  |
| **Chronic kidney disease** | K05 and K06 codes | N/A | eGFR based on serum creatinine using CKD-EPI equation (11) | N18, N19 |
|  |  |  |  |  |

Secondary outcomes: CVD risk and CVD risk factors, including: smoking, BP, total cholesterol, HDL and BMI. Data on medication prescription for antihypertensive drugs, lipid-lowering drugs, antiplatelet drugs and nicotine replacement therapy will be analysed by recording drug codes to chapter subheadings in the British National Formulary (chapter 2 for CVD drugs).

1. **Data/ Statistical analysis**

The proportion of participants with values recorded for five risk factors (blood pressure, total cholesterol, HDL, BMI and smoking status) will be evaluated. Risk factor values will also be assessed. Changes over time in prescription of drugs for CVD risk management, including antihypertensive, lipid-lowering, antiplatelet and nicotine replacement therapy, will be evaluated.

The association between NHSHC and changes in CHD, stroke, diabetes and CKD clinical events will be examined using Cox hazard and Poisson regression models. Person-time approach will be adopted, where the start date is the date of the check. Hazard ratios will be estimated using Cox proportional hazards models and incident rate ratio using Poisson regression model. The proportional hazard assumptions will be tested. Linear mixed models will be used to study changes in continues outcomes (BP, cholesterol and BMI measurements). Follow-up will be censored if a control participant receives a health check at a later date. The effect of deprivation will be evaluated. Potential effect modification from deprivation category will be evaluated by testing for an interaction of health check status and deprivation category.

1. **Plan for addressing confounding**

To control for potential cofounders, model covariates will include age, gender, ethnicity and deprivation indices.

1. **Plan for addressing missing data**

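### Prescribing started after an incident CHD or stroke event counts as risk management by default, which dilutes the uptake comparison, materially so for rarely started drugs such as antiplatelets

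*Protocol*

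**What the plan says.** Prescribing is a secondary outcome. Under Exposures, Outcomes and Covariates: "Data on medication prescription for antihypertensive drugs, lipid-lowering drugs, antiplatelet drugs and nicotine replacement therapy will be analysed". Data/Statistical analysis labels the purpose: "Changes over time in prescription of drugs for CVD risk management, including antihypertensive, lipid-lowering, antiplatelet and nicotine replacement therapy, will be evaluated". The Technical Summary fixes the clock and the event: "We will adopt a time-to-event framework with date of check as the start date to evaluate the onset of new prescriptions". No indication for the prescription is specified.

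The hypotheses give these outcomes a direction. Objective 1 expects that "greater changes in CVD risk factors, CVD risk score and CVD risk management follow the NHS Health Check than are observed in control participants". Objective 2 expects that deaths and clinical events, CHD and stroke among them, "may be lower in participants who received NHS Health Checks than control participants".

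At entry the Study Population section "excluded all patients who were ever treated with antihypertensive drugs (8531) or statins (1529) before the date of the check", and it also removes prior diabetes, CHD and stroke. It does not mention prior antiplatelet or nicotine replacement use. After entry, one censoring rule is stated: "Follow-up will be censored if a control participant receives a health check at a later date". Nothing says how a CHD or stroke event before the first prescription is handled.

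**The concern.** The Health Check is presented as a primary prevention programme, so the prescribing of interest is treatment started because a check found raised risk. A drug started after a heart attack or stroke means the opposite: prevention has failed for that person. The event definition, the time origin and the single censoring rule together merge the two.

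The merged part depends on CHD and stroke, which are primary outcomes that the protocol expects to differ between arms. Fewer events after the check would mean fewer event-triggered prescriptions in that arm, pulling the uptake ratio down. Objectives 1 and 2 therefore act on this measure in opposite directions. The bias does not need the programme to work. The Background notes that smokers may be under-represented among attenders, and smoking is not among the listed covariates, so lower event rates through selection alone would have the same effect. At stake is how objective 1 is read for prescribing, not the primary outcomes.

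**Working it through.** **Inputs from the protocol (power calculation):** control CHD rate 3 per 1,000 per year; risk ratio 0.85; 75,000 and 182,000 participants; three years; type 1 error 0.05 (two-sided used here).

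**Assumptions, not in the protocol:** stroke incidence; the share *s* of events followed by a first prescription; the control rate *a* of preventive starts; the true Health Check/control ratio *g* for preventive starts.

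**1. The protocol's own figure.** Three-year risks are 0.003 × 3 = 0.00900 in controls and 0.85 × 0.00900 = 0.00765 after a check. Expected CHD events are 182,000 × 0.00900 = 1,638 and 75,000 × 0.00765 = 574. The standard error of the log rate ratio is √(1/574 + 1/1,638) = 0.0485, so z = 0.1625/0.0485 = 3.35 and power is Φ(3.35 − 1.96) = 91.8%. A pooled two-proportion test gives 92.7%. The stated power above 90% reproduces, so these inputs are usable.

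**2. Absolute differential.** Let *e* be the control event rate. Event-triggered starts over T years are *s·e·T* in controls and 0.85·*s·e·T* after a check, a gap of 0.15·*s·e·T*.

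- CHD only, T = 3, *s* = 100%: 0.900% against 0.765%, a gap of 0.135 percentage points; at *s* = 50%, 0.068.
- CHD plus stroke assumed at 4.5 to 6 per 1,000 per year, T = 3, *s* = 100%: 0.20 to 0.27.
- Six years, about the longest follow-up the dates allow, at 3 to 6 per 1,000 per year and *s* = 100%: 0.27 to 0.54.

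**3. Effect on the ratio.** Observed ratio = (*g·a* + 0.85·*s·e*)/(*a* + *s·e*). A true ratio above 1 appears below 1 only if *g* < 1 + 0.15·*s·e*/*a*. With *s* = 100%:

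| Control preventive starts, per 1,000 per year (assumed) | Reversal if *g* is below: CHD only, 3 per 1,000 | Reversal if *g* is below: CHD + stroke, 6 per 1,000 (assumed) |
|---|---|---|
| 1 | 1.45 | 1.90 |
| 2 | 1.23 | 1.45 |
| 5 | 1.09 | 1.18 |
| 10 | 1.045 | 1.09 |
| 20 | 1.02 | 1.045 |
| 30 | 1.015 | 1.03 |

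For a commonly started class, take *a* = 20 per 1,000 and *g* = 1.5. The observed ratio is (30 + 2.55)/(20 + 3) = 1.415 with CHD only, and (30 + 5.1)/(20 + 6) = 1.35 with CHD plus stroke. That is dilution, not reversal.

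**4. A rarely started class: antiplatelets over three years.** Assume stroke at 1 or 2 per 1,000 per year with the same 0.85, *s* = 80% or 90%, and control preventive starts of 0.5%, 1% or 2%, giving 12 combinations. One of them: event risk (3 + 1)/1,000 × 3 = 1.2%, *s* = 80%, preventive starts 1%. Control starts are 1% + 0.96% = 1.96%, of which 49% follow an event. With *g* = 1.10, Health Check starts are 1.10% + 0.85 × 0.96% = 1.916%, so the observed ratio is 0.978.

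Over all 12 combinations, post-event starts are 32–73% of control starts, and:

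| True ratio *g* | Event ratio | Observed ratio | Below 1 |
|---|---|---|---|
| 1.00 | 0.85 | 0.89–0.95 | 12 of 12 |
| 1.10 | 0.85 | 0.92–1.02 | 9 of 12 |
| 1.50 | 0.85 | 1.03–1.29 | 0 of 12 |
| 1.10 | 0.95 | 0.99–1.05 | 3 of 12 |
| 1.10 | 1.00 | 1.03–1.07 | 0 of 12 |

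**The case against.** The protocol never says that post-event prescriptions are counted. The one censoring sentence is not a full list, since it also omits death, leaving the practice and end of data. Outcome-specific censoring is often left to an analysis plan, and none is at hand. This stands in part: counting is the default consequence of the text, not a declared choice. But the protocol does fix the time origin, the event and a censoring rule, and what counts as risk management is part of the outcome definition.

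A reader might infer that the direction of every treatment outcome can reverse. The documents do not support that. The 0.85 is the effect the study is powered to detect for CHD, not a forecast, and applying it to stroke is an assumption. Start rates and the treated share are also assumed. At 10 preventive starts per 1,000 per year or more, reversal needs a true ratio below about 1.045 (CHD only) or 1.09 (with stroke at the assumed rate). Nicotine replacement is less clearly event-driven.

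The 80–90% share also leans high: some events are fatal, some strokes are haemorrhagic, and some people will already be on the drug.

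Finally, all starts is a legitimate measure of total uptake. Preferring preventive starts is a choice of estimand, so the all-starts analysis should stay.

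**Conclusion.** The point holds as dilution, against the Health Check arm if events are commoner in controls. For statins and antihypertensives, assuming preventive starts are common, the effect is modest, with a differential of at most about 0.135 percentage points on the protocol's CHD inputs over three years. For antiplatelets, assuming preventive starts are rare, dilution can be material, and reversal is possible when the true uptake effect is small. None of the 12 antiplatelet combinations reverses at a true ratio of 1.5. If the event ratio is 1, only dilution towards 1 remains. The outcomes are secondary and the correction is cheap, so it is worth making but does not threaten the main analysis.

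**What to change.** Add to Data/Statistical analysis: in the time-to-first-prescription analyses of antihypertensive, lipid-lowering and antiplatelet drugs, follow-up in both arms is censored at the first CHD or stroke event. The result is then a cause-specific hazard ratio for primary-prevention starts among people still event-free. Take event dates from the same source as the analysis, so that the unlinked and linked analyses each use their own. Report post-event starts separately by arm, and keep the all-starts analysis as a sensitivity analysis.

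The event dates are already needed for the primary outcomes, so no new data are required. The cost is fewer prescribing events. The loss should be small for commonly started classes but could be substantial for antiplatelets: up to the 32–73% of control starts in the illustration. Some starts close to an imprecisely coded event date will be misclassified, a coding weakness that the Limitations section already acknowledges.
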